### Statistical analysis

2.13.

Main statistical analyses will be performed at the individual and group levels (pre vs. post, treatment vs. sham) (26). To examine the differences between the groups, we shall employ the *t*-test or Mann–Whitney test for continuous variables and the Pearson Chi-squared or Fisher’s exact test for discrete values. If a statistically significant result appears, the inequality factors will be considered as potential confounding factors in the final analysis of effectiveness. To account for any potential external influences, linear models or linear regression will be implemented on continuous dependent variables and logistic regression models on categorical dependent variables. The Chi-square test or Fisher’s exact test will be employed to document and assess unfavorable events (26). We will test outcomes on behavior (diagnosis, CRS-R score) and brain data (MRI/EEG). The proportion of responders and the effect size of treatment (*r*, Cohen’s *d*) will be calculated. We will use *t*-tests, Chi-square tests, ANOVA (for normally distributed data), and Wilcoxon test (for non-ordinal data), and mixed-effect regression models, depending on the tested outcomes. EEG and MRI analysis will be evaluated using SPM12 software^1^ and EEGLAB^2^ implemented in MATLAB 9.5 (MathWorks, Natick, MA, United States), respectively. All other statistical analyses will be conducted in SPSS software (version 25). All data will be adjusted to account for multiple comparisons and considered statistically significant if the value of *p* is lower than 0.05.

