### Participants and recruitment

2.2.

Participants will be recruited from the neurologic care unit. The study will be advertised at the bedside between April 2021 and December 2022. Researchers will select potential candidates by reviewing their medical records in the Computerized Patient Record System (CPRS) and communicate the details of this trial to their families. Following the agreement of the participants’ guardians, a neurologist will review them based on the eligibility criteria. Those who meet the criteria have been invited to join the experiment and must go through a neurological examination before being evaluated for rehabilitation. All study participants must give permission by their family members.

Patients who meet the following criteria will be deemed eligible for the trial: (1) age > 18 years, onset >28 days; (2) patients were assessed by using CRS-R (five times) as DoC (UWS, MCS−, and MCS+); (3) patients had not received central stimulants drugs within 48 h before enrollment; (4) no neuromuscular blockers were applied within 24 h prior to enrollment; and (5) no facial or ear pain, no recent ear-related injuries, no metallic prosthetics, and no pregnancy. Patients who meet the following criteria will be excluded from the trial: (1) personal or familial history of seizures and history of cardiovascular disease, with developmental neurological or psychiatric illness history; (2) untreated brain edema; (3) metal implants in the body; (4) unstable vital signs; and (5) contraindications: such as claustrophobia.

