### Sample size

2.3.

The main outcome index of this study is the CRS-R scale score, which is set as a paired experiment count, the sample estimation formula is as follow:
$$n=\frac{{\left(Z_{\alpha /2}+Z_{\beta }\right)}^{2*}\sigma^{2}}{\delta^{2}}$$

According to the results of previous studies (4), the estimated difference standard deviation is 15, and the difference is 10, set two-sided = 0.05, and the grasp degree is 90%. According to the sample size calculation formula, 24 subjects were needed. Considering the loss of visits and refusal, at least 30 subjects were needed. Therefore, 30 *VS*/UWS and MCS patients will be randomly selected for each sample group, with a total sample size of 90.

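### Pre-versus-post change is an unranked main analysis alongside active versus sham, and the stated 90% power belongs to the paired test, not to the randomised comparison

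*Protocol article*

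**What the plan says.** All references are to the protocol article.

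- **Section 2.13 (Statistical analysis)** opens with "Main statistical analyses will be performed at the individual and group levels (pre vs. post, treatment vs. sham". The two contrasts stand side by side and are not ranked. The section goes on to list between-group tests, covariate-adjusted linear and logistic models, ANOVA and mixed-effect models, and promises an adjustment for multiple comparisons without naming the method.
- **Section 2.3 (Sample size)** takes CRS-R as the main outcome, "which is set as a paired experiment count". Its inputs are "the estimated difference standard deviation is 15, and the difference is 10", "set two-sided = 0.05" and "the grasp degree is 90" per cent. The result is "24 subjects were needed", raised to 30 for losses and applied to each of three groups, 90 in total.
- **Sections 2.1, 2.4 and 2.5** describe a 1:1:1 randomisation to two active arms and an earlobe sham arm.
- **Section 2.2 (Participants and recruitment)** admits patients with "age > 18 years, onset >28 days". No upper limit on time since onset is given. Section 2.1 sets a 40-day study followed by half a year of observation.

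**The concern.** A pre-post change within one arm mixes any treatment effect with spontaneous recovery, concurrent rehabilitation and fluctuation in the patient's state. The sham arm is there to remove these, and a paired test within an active arm does not use it. Nor does a significant change in an active arm beside a non-significant one in sham show that the arms differ. While the two contrasts have equal standing, a positive pre-post result could be reported as a main result even if sham patients improved just as much.

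The sample size adds to this. The only power figure in the article is for the paired test, so a reader would take 90% as the power of the randomised comparison, which it is not. Both points bear on the trial's first aim, to gauge the effectiveness of taVNS.

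**Working it through.** **Inputs from section 2.3.** SD of the difference 15, difference 10, two-sided alpha 0.05, power 90%, 24 per group before loss and 30 after. The loss rate is not stated; 24/0.80 = 30 would correspond to 20%.

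**1. Reproducing the plan's figure.** The plan's formula is n = (z for alpha/2 + z for beta)² × SD² / difference².

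(1.960 + 1.282)² × 15² / 10² = 10.51 × 2.25 = 23.64, rounded up to 24. This matches. It is the one-sample formula for within-patient differences.

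**2. The same inputs for two parallel arms.** The formula gains a factor of 2: 2 × 23.64 = 47.3, so 48 evaluable per arm (49 with the t distribution). The plan's 24 is therefore not the number for active versus sham.

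**3. Power of one active-versus-sham contrast at the planned size.** Assumptions: the SD of change is 15 in each arm, and the 10 points are a net difference over sham. The test is a two-sample t-test on change, with noncentrality 10 / (15 × √(2/n)).

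| Evaluable per arm | Noncentrality | Power at 0.05 | Power at 0.025 |
|---|---|---|---|
| 30 | 2.58 | 72% | 61% |
| 24 | 2.31 | 62% | 50% |

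The 0.025 column is a Bonferroni split over the two active arms. It is an assumption, because section 2.13 names no method.

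**4. Illustration: paired test in one active arm when taVNS has no effect.** The SD is 15 and alpha is two-sided 0.05. The power of the paired t-test is computed with noncentrality (gain/15) × √n. The spontaneous gains are assumed.

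| Spontaneous mean gain | In SD units | n = 30 | n = 24 |
|---|---|---|---|
| 2 points | 0.13 | 11% | 10% |
| 4.5 points | 0.30 | 36% | 29% |
| 7.5 points | 0.50 | 75% | 65% |

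The nominal rate is 5%. At alpha 0.025 and n = 30, the 36% and 75% become 25% and 65%. Multiplicity adjustment lowers the rates but does not cure the fault, which is the missing control. The rates also depend on the SD: with an assumed SD of 5 and n = 30, a 2-point gain gives 56%.

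**The case against.** The strongest reply is that section 2.13 is mostly comparative. Straight after the opening line it turns to differences between groups, and factors found to be unbalanced are to be carried into the effectiveness analysis as confounders, which makes sense only for a between-group contrast. Section 2.9 checks that the three groups are alike on CRS-R at baseline, and section 2.7 keeps the analyst from knowing which group is treated. The opening line could mean pre-post for individuals and sham comparison for groups, or simply the two factors of a time-by-treatment model. The ranking of contrasts may also sit in a fuller document that is not shown.

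Much of this stands. A reader might infer that the trial will declare taVNS effective on a pre-post result alone; no section states such a rule. A reader might also take the 36% or 75% as the trial's false-positive rate. The documents do not support that either: they give no figure for spontaneous change, and at the protocol's SD those rates need mean untreated gains of 4.5 and 7.5 points, the latter three quarters of the planned difference. The entry rule sets a minimum time since onset with no maximum, so it does not show that patients enter early in recovery. Repeated CRS-R assessments at eligibility and in each period limit regression to the mean.

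Two things remain. On any of these readings the line still gives pre-post main status and does not rank it below the sham comparison. And the paired sample size is a stated figure, not an omission. Section 2.5 mentions two sessions, which might suggest an active-sham crossover as the source of the pairing, but sections 2.1, 2.3 and 2.4 describe three parallel groups, where the natural pairing is before and after.

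**Conclusion.** The point holds as a defect of specification and of stated power. The plan leaves room for an uncontrolled within-arm change to be read as efficacy, and its 90% power is for that paired test. For one active arm against sham at the planned size, power is about 72% with 30 per arm and 62% with 24 evaluable, and lower once multiplicity is handled.

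These power figures rest on an SD of change of 15 in each arm and a net difference of 10 over sham. Any improvement under sham that is counted within the 10 would reduce the net difference and the power. Baseline adjustment could raise power by an amount that cannot be computed from the documents. The spontaneous-change rates show only the direction and possible size of the problem.

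**What to change.** **Section 2.13.** State that efficacy is judged on the baseline-adjusted CRS-R difference between each active arm and sham, with its confidence interval. State that within-arm and individual-level pre-post changes are descriptive. Exploratory EEG, MRI and biomarker changes should likewise not serve as evidence of efficacy without the sham contrast.

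**Section 2.3.** Replace the paired justification with the power for that contrast at the planned size, giving the assumed SD of change and the multiplicity rule. If 90% is to be kept for a single contrast at 0.05 with the same inputs, 48 evaluable per arm are needed, or 48/0.80 = 60 per arm and 180 in total under an assumed 20% loss.

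**Cost.** A few sentences and no new data if the size stays at 90. The sponsor gives up the easier within-arm claim and has to report a lower power.

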### Randomization

2.4.

The study will utilize block randomization. The participants will be classified into either the “MCS group” or the “UWS/*VS* group.” All subjects will be randomly divided into the intervention group and control group in a 1:1:1 ratio. To ensure impartiality, a random number will be used to produce a random allocation order, this task will be handled by a person who is not involved in the trial. The order of random allocation will remain undisclosed to those assessing the outcomes and the statistician. After evaluating the baseline information of the suitable participants, their healthcare personals and therapists (including acupuncturists and cognitive therapists) will not know patients random number assigned.

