### Baseline data

2.9.

This study will collect descriptive data including gender, age, onset, weight, etiology etc. before randomization. The CRS-R was used to evaluate DoC’s consciousness level, and this will be applied initially to check if the three groups are the same prior to the intervention.

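### Baseline significance tests decide which factors count as confounders, so adjustment for baseline CRS-R is not secured; the cost is conditional bias and lost power, not overall type I error inflation

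*Protocol article*

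**What the plan says.** Section 2.13 (Statistical analysis) sets the group comparison: "To examine the differences between the groups, we shall employ the *t*-test or Mann–Whitney test for continuous variables", with chi-squared or Fisher tests for discrete variables. It then gives the consequence: "If a statistically significant result appears, the inequality factors will be considered as potential confounding factors in the final analysis of effectiveness".

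Section 2.9 (Baseline data) indicates that these are baseline comparisons. It says of the CRS-R that "this will be applied initially to check if the three groups are the same prior to the intervention".

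The next sentence of section 2.13 adds: "To account for any potential external influences, linear models or linear regression will be implemented on continuous dependent variables", with logistic regression for categorical outcomes. It names no covariate. Later in the section, mixed-effect models appear in a list of methods to be chosen by outcome, and the main analyses are described as pre versus post and treatment versus sham.

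Section 2.4 (Randomization) says "The study will utilize block randomization", and then "The participants will be classified into either the “MCS group” or the “UWS/*VS* group". Section 2.13 does not mention this class.

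**The concern.** In a properly randomised trial, any baseline difference between arms arose by chance, so a baseline test examines a null hypothesis already known to be true. Its p-value does not measure how strongly the factor predicts the outcome, yet bias and precision depend on that strength. A rule driven by these p-values can leave a moderate imbalance in a strong predictor unadjusted and adjust for a chance difference in an irrelevant factor. It also lets the data choose the form of the effectiveness model.

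Baseline CRS-R is the natural predictor of later CRS-R and is already collected. At stake are the accuracy of the treatment estimate in trials that happen to be imbalanced, and power in a trial with little to spare. This is a stated decision rule, not a detail left open, so an analysis plan that followed the protocol would inherit it.

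**Working it through.** **Inputs from the protocol article.** Section 2.3: SD 15, difference 10, two-sided 0.05, power 90%, 24 subjects, 30 per group after losses, 90 in all. Section 2.4: allocation 1:1:1.

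**Assumed, not in the document.** The correlation r between baseline and outcome CRS-R (0.3 to 0.8); the outcome gap between MCS and UWS/VS; a 0.05 threshold for the baseline tests, taken from the general threshold in section 2.13.

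**1. The plan's own figure.** (1.960 + 1.282)² × 15² / 10² = 23.64, rounded up to 24. 24 / (1 − 0.20) = 30, so 30 fits a 20% loss, a rate the article does not state. The figures reproduce. The formula is a paired one. With the same inputs, one active arm against sham at 30 per arm has about 73% power: (10/15) × √(30/2) = 2.58, and Φ(2.58 − 1.96) = 0.73.

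**2. What the baseline test can miss.** The smallest observed difference reaching p<0.05 is t(0.975, 58) × √(2/30) = 0.517 SD. Anything smaller is unflagged.

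**3. Shift in the estimate.** For an unflagged imbalance of 0.4 SD, the unadjusted estimate moves by r × 0.4 on raw post-scores and by (r − 1) × 0.4 on change scores. In SD of the raw score:

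| r | raw post-score | change score |
|---|---|---|
| 0.5 | +0.20 | −0.20 |
| 0.7 | +0.28 | −0.12 |
| 0.8 | +0.32 | −0.08 |

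**4. Error rates by simulation** (40,000 two-arm trials per setting, 30 per arm, bivariate normal). The rule was modelled as ANCOVA if the baseline t-test is significant, and otherwise a t-test on raw post-scores or on change.
- About 19% of comparisons have an imbalance of 0.3 to 0.5 SD. In these, type I error is about 6 to 10% on raw post-scores (r = 0.3 to 0.8). On change scores it is about 6 to 8% (r = 0.5 to 0.8), or about 9% at r = 0.3. Prespecified ANCOVA stays at about 5%.
- Over all comparisons, the rule's type I error is about 3 to 5%.

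**5. Power for a 0.5 SD effect, rule versus always-on ANCOVA.**

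| r | default raw post-score | default change score |
|---|---|---|
| 0.5 | 48% v 59% | 48% v 59% |
| 0.7 | 49% v 75% | 70% v 75% |
| 0.8 | 49% v 88% | 85% v 88% |

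**6. Power at the plan's own effect, 10/15 = 0.67 SD.** If 15 is the SD of the raw score, the rule gives 73%, 74% and 74% at r = 0.5, 0.7 and 0.8, against 83%, 94% and 99% with ANCOVA. If 15 is the SD of change, the ANCOVA residual SD is 15 × √((1 + r)/2). The unadjusted change comparison then has 73% power, against about 85%, 80% and 78% with ANCOVA (normal approximation).

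**7. The MCS and UWS/VS class.** If blocks are formed within class, the arms are balanced on it and the trigger would practically never admit it. Even 12/30 against 18/30 gives a chi-squared p of 0.12. With balance by design and class gaps of 0.5, 1.0 and 1.4 SD, leaving the class out gives type I error of 4.4%, 2.4% and 0.5%. For the 0.67 SD effect, including it raises power from 73% to 75%, 74% to 83%, and 78% to 94%.

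**The case against.** Four stronger readings are tempting, and the article does not support them.

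- **That covariates can enter only through a significant baseline test.** Section 2.13 says significant factors will be considered, and its next sentence permits regression with no significance condition. It does not say non-significant factors are excluded. What stands is that this sentence names no covariate, so it does not secure adjustment for baseline CRS-R.
- **That the trial's false-positive rate is inflated.** The 6 to 10% applies to a selected fifth or so of comparisons. Overall the rate is at or below nominal.
- **That a loss of 26 points of power (49% v 75%) is established.** That figure needs raw post-scores as the default and r = 0.7. The article fixes neither. Its pre versus post wording, the paired sample size formula and the mention of mixed models all leave room for analyses that use baseline. With change scores the loss at r = 0.7 is about 5 points and at r = 0.8 about 3. At r = 0.5 it is 11 points either way.
- **That imbalance in the randomisation class goes uncorrected.** If blocks are formed within class, which section 2.4 implies but does not say, there is no such imbalance. The silence of section 2.13 about the class could also be resolved in an analysis plan that is not shown.

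It is also fair to say that describing and comparing the arms at baseline is routine. The fault lies in letting the result select covariates.

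**Conclusion.** The point holds as a badly fixed method. Section 2.13 ties confounder selection to significance tests that section 2.9 places before the intervention, and nothing else in the article guarantees adjustment for baseline CRS-R. The harm is conditional bias when a moderate imbalance goes unflagged, together with lost power. For a 0.5 SD effect and r from 0.5 to 0.8, the loss is about 11 to 39 points if raw post-scores are compared and about 3 to 11 points if change scores are compared. These sizes rest on the assumed r and on which comparison is the default.

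For the MCS and UWS/VS class the point is conditional. If it was balanced by within-class blocks, omitting it makes the test conservative and costs some power, by an amount that depends on an outcome gap the article does not give.

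**What to change.** In section 2.13, delete the sentence that makes adjustment depend on a significant group difference. State the primary CRS-R model in advance: arm, baseline CRS-R, and MCS versus UWS/VS class, fitted for all patients whatever the baseline comparisons show. The baseline comparison in section 2.9 can stay as description, with a statement that it does not select covariates. Section 2.4 should say whether blocks are formed within class. Make the change before the group labels are disclosed.

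The cost is a change of wording and one or two degrees of freedom. Both covariates are already collected, so no new data are needed.

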**Discussion:**

Transcutaneous auricular vagus nerve stimulation as a painless, non-invasive, easily applied, and effective therapy was applied for treatment of patients with depression and epilepsy several decades ago. Recent progress showed that taVNS has behavioral effects in the consciousness recovery. However, there is no clinical evidence to support the effects of taVNS on brain activity. Therefore, we will design a randomized controlled trial to evaluate the effectiveness and safety of taVNS therapy for DoC, and explore neural anatomy correlated to taVNS during the consciousness recovery. Finally, this protocol also tests some biomarkers along with the recovery of consciousness.

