### Study design

2.1.

Ninety patients suffering from DoC will be chosen for this prospective, randomized trial which involves double-blinded assessments. The participants will be randomly divided into the intervention and control groups with an even distribution. The control group will be administered ear lobe therapy, in contrast to the intervention group which will receive the active taVNS. We will stimulate left cymba conchae for one group, the second group subjects will be stimulated left cymba 20 min and right cymba 20 min once a day. Because we have not seen the side effects from the clinical practice, and the right vagus nerves modulate the left hemisphere. This study will last 40 days and a half-year observation period will follow. CRS-R behavioral improvement will be monitored five times every 10 days. At the beginning and the end of the fourth period, the following tests will be carried out: EEG, MRI, and measurement of certain biomarkers related to brain injuries. All side effects during each treatment will be documented. This study will be implemented in Shanghai Yongci Hospital, and rehabilitation therapists are held accountable for following the standard operating procedure and evaluating the trial’s progress at all clinical sites. This trial is illustrated in Figure 1.

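### The blanket multiplicity adjustment does not exempt adverse events and, read as written, further lowers an already limited sensitivity to harm with 30 patients per arm

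*Protocol article*

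**What the plan says.** Section 2.13 (Statistical analysis) gives adverse events one sentence: "The Chi-square test or Fisher’s exact test will be employed to document and assess unfavorable events". No other method for assessing them is named. The section ends with a general rule: "All data will be adjusted to account for multiple comparisons and considered statistically significant if the value of *p* is lower than 0.05". It does not name the correction method or the set of tests that share it, and it makes no exception for adverse events.

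Safety is a declared aim. The Discussion paragraph of the Abstract says the trial is designed to "evaluate the effectiveness and safety of taVNS therapy for DoC".

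The arms were sized on the CRS-R alone. Section 2.3 states that "the estimated difference standard deviation is 15, and the difference is 10", arrives at 24 subjects, raises this to 30 for losses, and concludes that 30 "patients will be randomly selected for each sample group, with a total sample size of 90". No power or sample size is given for adverse events, and no expected rate. The nearest statement is in section 2.1, where the left-plus-right arm is explained partly by "Because we have not seen the side effects from the clinical practice".

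The Abstract and sections 2.1 and 2.10 also commit to recording adverse events throughout treatment.

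**The concern.** For efficacy, a multiplicity correction protects patients from a false claim of benefit. For harms, the more serious error is usually to miss a real excess, and a correction makes that error more likely. If adverse-event tests share a correction with the CRS-R, diagnosis, EEG, MRI, P-tau and NFL, every added efficacy or biomarker test raises the bar for seeing harm.

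Taken literally, the closing rule of section 2.13 does this. What is at stake is how sensitive the safety comparison is in a trial that says it evaluates safety, with arms that were not sized for that purpose.

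**Working it through.** **The plan's own figure.** Section 2.3 uses n = (z for 0.975 + z for 0.90)² × SD² / difference². With z values 1.960 and 1.282, SD 15 and difference 10, this is 10.507 × 225 / 100 = 23.64, rounded up to 24. Allowing 20% loss (implied, not stated), 24 / 0.80 = 30. The stated figures reproduce, but they concern the CRS-R only.

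**Inputs for adverse events**
- Arm size 30; two active arms and one sham arm (sections 2.3 and 2.4).
- Test: Fisher's exact or Pearson chi-square (section 2.13).
- Threshold: 0.05 uncorrected. The corrected threshold is an assumption: Bonferroni over three pairwise contrasts, 0.05 / 3 = 0.0167.
- Event rates: assumptions, shown over a range.

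**Single tables (Fisher, two-sided)**
- 5/30 versus 0/30: p = 0.052, so it misses 0.05 without any correction.
- 6/30 versus 0/30: p = 0.0237, significant alone; 3 × 0.0237 = 0.071 after correction.
- With no sham events, 6 active events are needed at 0.05 and 7 at 0.0167.

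**Exact power.** Power = sum over all pairs (a, s) of Bin(a; n_active, p_active) × Bin(s; n_sham, p_sham), counting only tables with p below the threshold and the higher proportion in the active group.

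| Active v sham rate | Fisher, 30 v 30: 0.05 → 0.0167 | Chi-square, 30 v 30: 0.05 → 0.0167 | Fisher, pooled 60 v 30: 0.05 → 0.0167 |
|---|---|---|---|
| 20% v 2% | 40.5% → 26.0% | 69.5% → 39.9% | 67.2% → 41.7% |
| 20% v 5% | 24.1% → 13.6% | 45.3% → 22.3% | 40.3% → 20.1% |
| 30% v 5% | 63.1% → 46.5% | 77.8% → 58.7% | 83.6% → 64.5% |

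The expected number of events per arm under no difference is 30 × (0.20 + 0.02) / 2 = 3.3, 30 × (0.20 + 0.05) / 2 = 3.75 and 30 × (0.30 + 0.05) / 2 = 5.25. By the usual rule of at least 5, Fisher would be chosen in the first two rows, and chi-square is usable in the third.

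**How much is due to the correction?** Take the plan's 90% CRS-R power as a yardstick, for comparison only. The Fisher shortfall at 30 v 30 before any correction is 90 − 40.5 = 49.5, 90 − 24.1 = 65.9 and 90 − 63.1 = 26.9 points. The correction adds 40.5 − 26.0 = 14.5, 24.1 − 13.6 = 10.5 and 63.1 − 46.5 = 16.6 points. In each row the sample size accounts for more of the shortfall than the correction does.

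**What an interval would show.** With zero events, the exact two-sided 95% upper limit is 1 − 0.025^(1/n): 11.6% for n = 30 and 6.0% for n = 60.

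**The case against.** The closing rule is one loosely worded sentence that follows the sentences on imaging, EEG and statistical software, and adverse events have their own sentence earlier. It may have been meant for efficacy and brain data only. Since no family or method is given, the three-contrast Bonferroni is the reviewer's assumption. This stands as a caution about size. It does not remove the point, because the words cover all data and nothing exempts harms.

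Low power for harms is normal in a trial sized for efficacy and is not an error of the plan. This also stands: exempting adverse events recovers only the part of the loss that the correction causes.

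A reader might infer that a real excess of harm would usually be reported as no difference, or that a non-significant test is the only basis for a safety statement. The document says neither. It commits to recording events and does not limit reporting to p-values. The word usually also fails under permitted choices: for 30% versus 5%, corrected power is 59% with chi-square and 65% with Fisher on pooled active arms.

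The remark in section 2.1 about side effects explains the choice of arms and is not a safety conclusion. Detailed event tables and the wording of conclusions are commonly left to an analysis plan, so their absence is not counted here.

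**Conclusion.** The point holds in a limited form. Section 2.13 tests adverse events for significance and then applies to all data a correction that does not exempt them. Followed as written, this lowers the sensitivity to harm in a trial with a stated safety aim.

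Under the three-contrast Bonferroni and the rates assumed above, the cost is about 10 to 17 percentage points of Fisher power at 30 versus 30. A larger family would cost more: over ten tests (threshold 0.005), power for 20% versus 2% falls to 14%. For very large excesses power stays high despite the correction, for example 82% for 50% versus 10% at 0.0167.

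The correction worsens a limitation that comes mainly from the arm size. The documents do not support a claim that the plan would report harm as absent.

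**What to change.** In section 2.13, restrict the closing rule to efficacy outcomes and state that adverse events are exempt from the multiplicity adjustment.

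Add that adverse events will be reported for each of the three arms, and for the two active arms pooled, as numbers and percentages of patients with exact 95% confidence intervals, together with risk differences versus sham. Chi-square or Fisher p-values can stay, labelled unadjusted and descriptive. State that a non-significant result will not be taken as evidence of safety. The interval then shows what 30 or 60 patients cannot exclude, which deals with the sample-size part that the exemption leaves untouched. Table layouts can be left to the analysis plan.

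The cost is a few sentences and one table, with no new data and no change to trial conduct. The small downside is that some chance imbalances in adverse events will appear without correction.
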